### Data Management

Survey data are collected on laptop computers connected to Research Electronic Data Capture [35], a secure cloud-based Web app for data capturing in both online and offline settings, managed by the University of Miami. On a monthly basis, data are reviewed by the study statistician for missing or out-of-range values and potential inconsistencies. As needed, these discrepancies are reviewed with the study team and statistician.

### Sample Size and Statistical Power

We reviewed stroke and cardiovascular intervention programs to estimate the sample size required for this study [21,46]. Sample size consideration and power analyses were performed based on the primary outcome variable of systolic blood pressure. Using an SD of 21 mm HG with an alpha significance level of.05 and two-sided *t* test analyses, we estimated that 150 participants per study arm (300 participants total) could detect a minimum difference of 8 mm HG between groups with 91% power. This is smaller than the 10 mm Hg threshold in secondary stroke prevention guidelines [47]. For our secondary outcome of low-density lipoprotein), we will have 80% power to detect a minimum low-density lipoprotein difference of 13 mg/dL given SD of 39 mg/dL. For adherence to antiplatelet or antithrombotic therapy, we will have 83% power to detect a 15% difference in adherence among the intervention versus control group. All data will be analyzed using the latest SAS software (Cary, NC).

### Primary Outcome

The primary outcome is a change in systolic blood pressure from baseline to the 12-month evaluation as measured using the Omron HEM-705CP automated oscillometric device (Lake Forest, IL, USA). Following the American Heart Association guidelines, 3 readings are taken, and the average of the last 2 readings is used as the blood pressure measurement [48]. The study is powered to test the hypothesis that at 1 year, systolic blood pressure of participants enrolled in the intervention will be 8 mm HG lower than those in the control (see below).

### Secondary Outcomes

Secondary outcomes are low-density lipoprotein, glycated hemoglobin (for diabetic participants), and adherence to antiplatelet or antithrombotic medications (for ischemic or embolic stroke patients). To assess low-density lipoprotein and glycated hemaglobin, a certified phlebotomist obtains 10 cc of blood. Samples are spun and delivered to the University of Miami Diabetes Research Institute for lipid profiling. Glycated hemaglobin analyses are performed via latex agglutination, and low-density lipoprotein is estimated using the Friedewald equation [49]. For those with triglycerides greater than 400 mg/dl, a direct low-density lipoprotein measurement is performed. Self-reported medication adherence is assessed using the Morisky Medication Adherence Scale [50].

### Confounding Variables

Potential confounders of our primary and secondary outcomes include sociodemographics (age, sex, income, and educational attainment); health insurance status; depression (Center for Epidemiological Studies Depression Scale) [51]; acculturation (modified Marin-Marin scale) [52,53]; health literacy (Short Assessment of Health Literacy-Spanish and English) validated in both English and Spanish) [54]; body mass index; and functional status (modified Rankin score) [32].

### Mechanistic Variables

Mechanistically, we expect the CHW intervention to be successful in blood pressure management through 2 primary pathways. The first is through better medication management. Although the intervention team is not involved in managing medications, our behavioral intervention can result in improved medication management through either increased medication adherence or by ensuring that patients have an appropriate and timely follow-up with their existing primary care providers who manage medications. The second is through lifestyle changes, primarily diet and exercise.

To conduct potential exploratory analyses of how the intervention may have resulted in improved outcomes, we are collecting data on potential mediators including medication adherence, medication intensification, salt intake, physical activity, and provider visits. This will allow us to examine the degree to which any improvements in blood pressure were mediated by changes in these variables. We are also collecting detailed data on service intensity. We can then examine the correlations between blood pressure control and items such as number of home visits, telephone calls, and group visit participation. Similarly, items in the cell phone intervention can also be correlated with blood pressure control, such as the number of days in which blood pressure values were uploaded or frequency of SMS text messaging responses. A summary of variables being collected is shown in Table 1.

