### Intervention Enhancement Phase (Months 1-4)

Conceptually, we divided the CHW intervention into the following 2 phases: the enhancement phase, which consists of individualized health education, and the maintenance phase. The enhancement phase occurs during the first 4 months and includes home visits and phone calls. Although the number of home visits and phone calls is based on individualized decisions, as a rough, estimate we plan 5 home visits in this 4-month period and 2-3 phone calls per month. Although the length of calls is determined by CHW, it is expected that most calls would average under 15 minutes. In this phase, CHW helps the participant identify the issues that may affect his or her overall health and well-being. These can include direct influences, such as comorbid health conditions and behavioral risk factors, or more indirect influences, such as socioeconomic status and social context, poor health literacy, barriers in communication, and limited experience navigating the health care system. Once these barriers are identified, participants can then develop structured goals and methods for overcoming these obstacles in a manner that aligns with their needs and preferences.

CHW guides participants through this process by developing individualized health and well-being plans. This includes orienting participants on the principles of self-management and engaging them in a problem solving process that sets priorities for immediate problem resolution. To ensure that participants achieve their personal health goals regarding stroke risk and related risk factors, each CHW is tasked with a number of roles including, but not limited to, health and behavior counseling and coaching, medical service navigation (eg, scheduling appointments, sending reminders, providing guidance through the health system bureaucracy, etc), and social support (eg, identifying local social resources programs such as immigration services, tenant advocacy, and domestic violence programs). A major component of health education consists of blood pressure home self-monitoring. For participants who do not have a home blood pressure meter, CHWs help by providing one at no cost to them. However, data from these monitors will not be used for the outcome analyses. Those will be based on the blood pressure readings obtained during a structured assessment at 12 months, as described below.

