**Additional training:**
Florida Community Health Worker Coalition-Partnership to Train Community Health Workers in Patient-Centered Research (a 7-hour course on research training for community health workers developed with support from the Patient-Centered Outcomes Research Institute)Patient-centered outcomes research: rationale, definitions, role of community health workersClinical trials: types, randomizationData collection methods: qualitative and quantitative methods, avoiding biasInformed consent processStudy protocol and reporting: working in a research teamDisseminating study results: to study participants, how community health workers can contribute to research manuscriptsEthics: Institutional Research Boards, privacy and confidentiality, professional boundariesNational Institutes of Health Community Health Worker Health Disparities Initiative Health Education Materials & ResourcesSu corazón, su vida: Manual del promotor y promotora de saludHealthy Heart, Healthy Homes seriesSalud para su Corazón: Bringing Heart Health to Latinos - A Community Program Guide for LatinosApproaches to Enhance Learning: Using Adult Learning and Popular Education with the National Heart, Lung, and Blood Institute Heart Health Curricula (webinar)Improving Heart Health with Community Health Workers, Promotores, and Community Educators (webinar)

An important component of the queries is that participants are asked to enter their blood pressure. These data are processed and organized into 3 response categories, namely, high risk (requires immediate attention, systolic blood pressure >180 mm HG), moderate risk (requires attention, systolic blood pressure >140 mm HG), and low risk or normal (systolic blood pressure <120 mm HG). These thresholds were based on existing guidelines at the time of the study [45] and clinician input (OC and JGR). For high-risk participants, the system alerts the patient to contact their physician or CHW; further, it sends the patient’s name to CHW so that they are aware that the patient requires a call that same day. In consultation with project physicians (OC, JGR, SD), CHWs decide a plan of action for such participants. This may include an emergency room referral.

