Participants at moderate risk are provided with automated feedback. The data also alert CHWs of participants that may require additional follow-up. This information is valuable in helping CHWs further pinpoint the areas of concern, thereby creating a more focused and effective intervention strategy; for example, this may include calling participants and asking about medication adherence or recent changes in diet. When needed, CHWs can also alert the patients’ health care provider about patent blood pressure readings that remain high over several days. They can also help obtain an urgent appointment for such patients to see their primary care provider. CHWs and study team staff do not engage in medication management. When needed, they facilitate contact and interaction with the participant’s primary care provider who then decides if medication changes are needed.

Training of participants in the mHealth intervention is conducted by CHWs. The training includes how to interface with the study’s text support system, how to submit daily blood pressure readings, and how to use the various medication, diet, and physical activity reminders built into the system. In general, training of participants takes less than 60 minutes but varies depending on the patients’ baseline level of mobile phone use. Participant caregivers are also invited to participate in the training so that they may also be able to assist in the device usage or, in some cases, become the primary user of the technology for the participant.

With respect to data privacy, users are assigned a unique name for identifying and tracking user identity, and the server does not transmit or store any identifying information. In addition, user sessions are terminated after 15 minutes of inactivity. Data within the database server are encrypted using Transparent Data Encryption, which protects data at rest and data that are being transmitted over an electronic communications network using 256-bit encryption.

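### The exploratory correlation of blood pressure control with number of contacts is confounded by indication, because high readings during follow-up prompt extra calls

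*Protocol article*

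**What the plan says.** The Mechanistic Variables section of the protocol article introduces its plan with "To conduct potential exploratory analyses of how the intervention may have resulted in improved outcomes" and, after mediation, turns to the amount of contact delivered: "We can then examine the correlations between blood pressure control and items such as number of home visits, telephone calls, and group visit participation". It adds that days of blood pressure upload and text-message responses can be correlated with control in the same way.

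The delivery sections show how contact numbers arise:

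- Intervention Enhancement Phase (Months 1-4): "Although the number of home visits and phone calls is based on individualized decisions", with a planning figure: "as a rough, estimate we plan 5 home visits in this 4-month period and 2-3 phone calls per month".
- Maintenance Phase (Months 4-12): weekly calls for everyone, with further home visits possible.
- Mobile Technology Component (text after the training box), uploaded systolic reading above 180: the system alerts the patient, and the health worker is made "aware that the patient requires a call that same day".
- Same section, moderate-risk readings (above 140): "The data also alert CHWs of participants that may require additional follow-up"; for example, "this may include calling participants and asking about medication adherence or recent changes in diet".

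The mobile component is optional within the intervention arm. The Statistical Analysis section lists age, sex, body mass index and education as covariates, with some others to be explored. On-study blood pressure is not among them, and nothing separates routine from prompted contacts.

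**The concern.** A correlation between contacts and control is informative about how the intervention works only if contact numbers are not themselves set by blood pressure. Here they partly are. A participant whose pressure stays high during follow-up uploads high readings, receives more calls, and is also more likely to be uncontrolled at 12 months. That is confounding by indication, created by the delivery rules. Adjusting for one baseline reading does not remove it, because the trigger is pressure during follow-up.

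At stake is a secondary message, not the trial's main result: a report could say that more health-worker contact goes with worse control, or that contact intensity does not matter, when each contact helps. The Limitations section stresses cost per patient and relevance to policy makers, so readers may take an interest in such a finding.

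A smaller point concerns the same sentence. It lists group visits, but the intervention sections describe only home visits, telephone contact and text messaging.

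**Working it through.** **The plan's own figure.** The protocol gives no number for this analysis. The related figure is the power for the primary outcome: SE = 21 × √(2/150) = 2.425; 8/2.425 = 3.299; Φ(3.299 − 1.960) = 0.910. This reproduces the stated 91% and is not in dispute. It supplies the SD of 21 used below.

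**Routine contacts implied by the protocol.** Months 1-4: 5 visits + 4 × (2 to 3) calls = 13 to 17. Months 4-12: weekly calls for 8 months, 8 × 52/12 ≈ 35. Total about 48 to 52; 50 is used.

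**Illustrative model (assumptions, not from the documents).** Underlying systolic pressure S has mean 140 and SD 15. Measured SD is 21, so error variance is 441 − 225 = 216. Total contacts C = R + T. Routine contacts R are unrelated to S. Alert-driven calls T are Poisson with mean t × (S − 140) when S > 140, otherwise 0. Each contact truly lowers 12-month pressure by 0.40 mm Hg.

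- Mean of T = 15t/√(2π) = 5.984t, which is 0.60 calls at t = 0.1 and 1.20 at t = 0.2.
- k = Cov(T, S) = 225t/2, which is 11.25 or 22.5.
- Var(T) = 5.984t + 225t²(1/2 − 1/(2π)) = 5.984t + 76.69t², which is 1.365 or 4.264.
- Raw slope = −0.40 + k/Var(C).
- Slope adjusted for baseline reading = −0.40 + 216k/(441·Var(C) − k²).

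| Routine contacts | t | Var(C) | Raw slope | Baseline-adjusted slope |
|---|---|---|---|---|
| Mean 50, Poisson | 0.1 | 51.365 | −0.18 | −0.29 |
| Mean 50, Poisson | 0.2 | 54.264 | +0.01 | −0.19 |
| Mean 50, SD 3 | 0.1 | 10.365 | +0.69 | +0.15 |
| Mean 50, SD 3 | 0.2 | 13.264 | +1.30 | +0.51 |

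Slopes are mm Hg per contact; the true value is −0.40. In this model the mean number of contacts does not matter, only their variance. Uniform weekly calls make low variance plausible, but the protocol gives no figure. If only 60% take up the mobile component (assumed), the Poisson rows become −0.27 and −0.15 (simulated).

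**On the scale the protocol names.** A different simulation used 15 routine contacts, a mean benefit of 8 mm Hg, 5 to 20 extra contacts per threshold crossed, and correlations of 0.3 to 0.7 between baseline, on-study and 12-month pressure. The correlation of contacts with control (12-month systolic below 140) moved from +0.08 without triggering to between −0.02 and −0.31. In a variant with 5 routine contacts and readings close to baseline, a correlation of 0.3 gave only attenuation. The sign reversed at 0.5 with 4 or more extra contacts per threshold, or at 0.7 with 2 or more.

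**Routine contacts only.** If R is unrelated to S, the slope on R returns −0.40. If R itself rises by 0.05 per mm Hg of S, then Cov(R, S) = 0.05 × 225 = 11.25 and Var(R) rises by 0.05² × 225 = 0.56. The omitted calls T scale the bias by 1 − 0.40 × 11.25/225 = 0.98 (t = 0.1). The baseline-adjusted slope is then:

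- Poisson: −0.40 + 0.98 × 216 × 11.25/(441 × 50.56 − 126.6) = −0.29.
- SD 3: −0.40 + 0.98 × 216 × 11.25/(441 × 9.56 − 126.6) = +0.18.

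Separating the calls helps but does not guarantee an unbiased answer.

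**Change from baseline.** In the table's model, change = −0.40C plus measurement error, so its slope is the true −0.40. This depends on the model: if contacts respond to the baseline reading itself, regression to the mean exaggerates the benefit.

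**The case against.** The strongest reply is that this is one permissive sentence about an optional exploratory analysis in a condensed article. It names no estimator, adjustment set or dose-response claim, and such detail commonly sits in an analysis plan. That limits the weight of the point but does not remove it: the article does name the outcome, the exposure and the purpose, and that exposure conflicts with its own delivery rules.

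Several limits stand:

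- Only readings above 180 require a call. Above 140 a call may follow.
- Automatic alerts reach only those who opt into the mobile component.
- No text has a reading trigger a home visit. Individualization in months 1-4 is described in terms of barriers, goals and needs, not pressure level.
- Engaged participants may accept more contact, upload more and reply more, which biases in the opposite direction.

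A reader might infer that an effective intervention will look harmful. The documents do not support that. The effect of the intervention is judged by comparing randomized arms, which this analysis does not touch; only the within-arm association can mislead. Nor is reversal certain: with 50 routine contacts varying as Poisson, the result is attenuation, to about zero at the higher trigger rate.

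**Conclusion.** The point holds as a limited one. The planned within-arm correlation of control with contact counts is confounded by indication, and the alert rules pull it toward more contact, worse control. Against an assumed true slope of −0.40 mm Hg per contact, and with an average of about one alert-driven call or fewer per person, the raw slope runs from −0.18 to +1.30. The result turns on the unstated trigger rate and on how much routine contacts vary. Baseline adjustment alone leaves −0.29 to +0.51. These figures illustrate direction and sensitivity; they do not predict this trial's result, and the net direction after any opposing engagement bias cannot be settled from the document. The primary and secondary randomized comparisons are unaffected. The repair is worth making because it is cheap and the sentence as written invites a misleading reading. The group-visit item is a minor wording inconsistency.

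**What to change.** In Mechanistic Variables, replace the correlation with total contacts as follows:

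1. Use the dashboard alert records and the service-intensity data already collected to separate calls that follow a blood pressure alert from routine contacts. This assumes that those records allow alerts and calls to be matched, for example by date. A new log field could not recover contacts made since enrollment opened in February 2015.
2. Relate outcome to routine contacts only, using 12-month systolic pressure adjusted for baseline, with change from baseline as a sensitivity analysis, instead of control status alone.
3. Report alert-driven calls, upload days and text-message responses descriptively.
4. State that all these associations are non-causal, because routine contacts are also individualized and some bias remains.
5. Reconcile the mention of group visits with the intervention description, which contains none.

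The cost is a few sentences of wording and a matching step on existing records. The downside is less variation in the exposure and wider intervals on an exploratory estimate.

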### Statistical Analysis

The distribution of baseline values and outcomes will be examined for each arm. The intervention effects on outcomes (systolic blood pressure, low-density lipoprotein, and glycated hemaglobin) will be evaluated using linear regression models for continuous variables as a function of intervention status as well as with categorical classification variables to index time intervals pre- and postintervention. We will use statistical tests of the estimates of the regression parameters from this model to compare the major outcomes before and after the intervention groups in the full sample as well as between intervention groups. Adherence to antiplatelet or antithrombotic therapy will also be evaluated using logistic regression models as a function of intervention status. Covariates that will be included in the models will include age, sex, body mass index, and educational attainment. Relationships between the outcome variables and other potential covariates such as income, health insurance status, health literacy, and functional status will be explored to determine their potential inclusion in final models.

**Table 1 table1:** List of variables and measures included in Hispanic Secondary Stroke Prevention Initiative baseline survey.

Variables		Measures or methods

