### Randomization and Blinding

Patients are randomized at a 1:1 ratio to the enhanced care group or the CHW intervention group within each hospital. Within each site, every eligible patient receives a unique study subject identification number and the prespecified assignment that corresponds to the identification number through randomization. The principal investigator and the program clinical coordinator are blinded to study allocation. However, both participants and CHWs are aware of the group to which each participant was randomized.

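### The stated regression model does not identify which coefficient tests the 12-month blood pressure hypothesis, or how paired readings and baseline pressure enter the analysis

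*Protocol article*

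**What the plan says.** All references are to the protocol article.

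- **Primary Outcome:** "The primary outcome is a change in systolic blood pressure from baseline to the 12-month evaluation". The same section gives the powered hypothesis as a between-arm difference of 8 mm Hg at one year.
- **Sample Size and Statistical Power:** the calculation is a t test of two groups with SD 21 mm Hg, "150 participants per study arm (300 participants total"), which "could detect a minimum difference of 8 mm HG between groups with 91% power". It does not say whether 21 is the SD of the 12-month value or of the change.
- **Statistical Analysis:** continuous outcomes are modelled by linear regression "as a function of intervention status as well as with categorical classification variables to index time intervals pre- and postintervention". Tests of the model's parameters will then be used to "compare the major outcomes before and after the intervention groups in the full sample as well as between intervention groups". The fixed covariates are age, sex, body mass index and education. The baseline value of the outcome is not among them.
- **Limitations:** the only method for correlated data in the article is weighted generalized estimating equations. It appears as one possible sensitivity analysis for dropout.

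**The concern.** Time indicators for before and after make sense only if baseline and 12-month readings both sit in the outcome column, giving two rows per participant. The section therefore goes as far as naming the model family, the terms and the covariates, but it stops short of the one item that ties the model to the primary outcome: the coefficient to be tested.

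This is not a cosmetic gap, because the terms that are named do not contain the required contrast. With arm and time as main effects only, the arm coefficient averages the baseline difference and the 12-month difference, and the time coefficient pools the two arms. The between-arm difference in change is the arm-by-time term, which is not mentioned. How the two readings of one person are linked also decides whether the standard error is right, and the main analysis is silent on that too.

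An analyst following the sentence could reach different estimates and different error rates for the only primary analysis described. The sentence also lists a before-after comparison in the full sample next to the between-arm comparison without ranking them. The pooled comparison carries no between-arm information.

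**Working it through.** **Inputs from the article:** 150 per arm, difference 8 mm Hg, SD 21 mm Hg, two-sided alpha 0.05 (Sample Size and Statistical Power); 1:1 allocation (Randomization and Blinding).

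**Assumed, not in the article:** within-person correlation ρ between the baseline and 12-month readings of 0.3, 0.5 or 0.7; SD 21 at both visits; complete data; no further covariates.

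**1. The plan's own figure.** SE = 21 × √(2/150) = 2.42. Power = Φ(8/2.42 − 1.96) = 91.0% (noncentral t: 90.8%). The stated 91% reproduces.

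**2. Arm and time main effects, independent rows.**
- Randomization makes the expected baseline difference 0, so the arm coefficient targets (0 + 8)/2 = 4 mm Hg.
- SE reported by ordinary least squares: 21 × √(1/150) = 1.71.
- True SE: 21 × √((1 + ρ)/150).
- Type I error: 2 × [1 − Φ(1.96 × 1.71 / true SE)].
- Power: 1 − Φ((1.96 × 1.71 − 4) / true SE).

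**3. Arm-by-time interaction, independent rows.**
- The target is the full 8 mm Hg.
- SE reported: 21 × √(4/150) = 3.43.
- True SE: 21 × √(4(1 − ρ)/150).
- Type I error and power follow as in step 2, with 3.43 for 1.71 and 8 for 4.

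**4. Same interaction contrast with the correct SE** (equal to a comparison of change scores). Power = Φ(8 / true SE − 1.96).

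**5. 12-month value adjusted for baseline.** SE = 21 × √(2(1 − ρ²)/150). Power = Φ(8/SE − 1.96).

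| | ρ = 0.3 | ρ = 0.5 | ρ = 0.7 |
|---|---|---|---|
| Step 2: true SE (reported 1.71) | 1.95 | 2.10 | 2.24 |
| Step 2: type I error | 8.6% | 11.0% | 13.3% |
| Step 2: power | 63% | 62% | 61% |
| Step 3: true SE (reported 3.43) | 2.87 | 2.42 | 1.88 |
| Step 3: type I error | 1.9% | 0.6% | 0.03% |
| Step 3: power | 67% | 70% | 75% |
| Step 4: power | 80% | 91% | 99% |
| Step 5: SE | 2.31 | 2.10 | 1.73 |
| Step 5: power | 93% | 97% | >99% |

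**6. Simulation check.** With 4,000 simulated trials per scenario, the step 2 model gave mean effects of 3.99 to 4.04 mm Hg, type I error of 8.4%, 11.2% and 13.1%, and power of 61% to 63%. The step 3 model gave mean effects of 8.00 to 8.09 mm Hg, type I error of about 2.1%, 0.6% and 0.03%, and power of 68%, 71% and 75%.

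**7. Sensitivity to the assumptions.** The halving in step 2 involves neither ρ nor the SD. The type I errors depend on the ratio of reported to true SE, which is 1/√(1 + ρ) in step 2 and 1/√(1 − ρ) in step 3. They therefore change with ρ, but not with the size of an SD common to both visits. The power figures change with both.

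**The case against.** A reader might infer that the plan commits to main effects with independent rows, so that the trial will report half its effect with a wrong standard error. The documents do not support that. Nothing in the Statistical Analysis section rules out an interaction, a repeated-measures covariance or robust standard errors. The closing words of "compare the major outcomes before and after the intervention groups in the full sample as well as between intervention groups" can be read as comparing the before-after change between arms, which needs an interaction. The Primary Outcome and sample size sections both point to a between-arm difference at one year, so a model that targets half of it would contradict the stated hypothesis. Covariance details are also the kind of content that a condensed article leaves to a fuller plan. All of this stands.

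Two further inferences fail. The 91% power is not wrong: it reproduces for the test it describes. And no passage makes the pooled before-after comparison the primary test.

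The harm is also uneven. Inflated type I error arises only under the main-effects reading. The interaction reading with independent rows loses power but does not favour a false claim of benefit. The calculations also leave out the four listed covariates.

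What remains is that the article does set out the model's terms, and those terms do not contain the contrast that the primary outcome calls for. Mentioning weighted estimating equations as an option for dropout does not say how the main analysis treats paired readings.

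**Conclusion.** The point holds as a lack of identification. The article states a model for the primary outcome without naming the coefficient that tests it, without the baseline value as a covariate and without any treatment of the paired readings. It does not show that the intended analysis is invalid.

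The size depends on how the sentence is carried out. Main effects with independent rows would target 4 instead of 8 mm Hg, with type I error of about 9% to 13%. An interaction with independent rows would be unbiased, with type I error of 2% or less and power of about 67% to 75%. A baseline-adjusted comparison would target the full 8 mm Hg with power from 93% to above 99%. The error and power figures rest on the assumed correlation of 0.3 to 0.7 and on SD 21 at both visits, neither of which the article states. The halving does not rest on the correlation.

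Because the remedy is free and gives one unbiased, efficient contrast, it is worth making even if the authors already intended a correct model.

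**What to change.** - State the primary analysis as a linear regression of 12-month systolic pressure on arm and baseline systolic pressure, plus the covariates already listed, with one row per participant.
- Alternatively, keep both rows and use the arm-by-time contrast from a repeated-measures model with within-participant covariance. This targets the same difference. It matches the precision of the baseline-adjusted analysis if the baseline means are held equal across arms; without that constraint it has the change-score power in step 4.
- Name that between-arm contrast at 12 months as the sole test of the primary hypothesis.
- Use the same structure for low-density lipoprotein and glycated hemoglobin.
- Label the full-sample before-after comparison descriptive.

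The cost is wording in the Statistical Analysis section. Blood pressure is already measured at baseline and at 12 months, so no new data are needed and the sample size does not change.
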